#### Statistical analysis

Analysis will be by intention to treat. Differences between groups will be estimated using the appropriate methodology depending on the distribution of data, either by *t* test or Wilcoxon test at the 5% significance level to compare the distribution of the primary endpoint between the treatment samples. The patient outcome scores will be assessed with repeated measures analysis of variance (ANOVA) models to account for the repeated data collection time points. Results will be presented as an adjusted mean difference with its corresponding 95% confidence intervals.

Should significant data volume be missing at random, we will incorporate a complete case analysis in addition to intention to treat. If there are concerns as to the balance of data in the trial arm, we will run sensitivity analyses. Subgroup analysis is planned by femur type (Dorr classification). Any further subgroup analysis will be post-hoc and clearly labelled as such. A data analysis plan will be finalised prior to data lock and the analysis will be conducted blind to intervention allocation.

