## Methods

### Study aim

The primary objective of the ‘Can Arthroplasty Stem INfluence Outcome?’ (CASINO) study is to assess whether using the 125 mm Exeter V40 stem in total hip arthroplasty achieves an equivalent change in patient-reported pain and function as the 150 mm Exeter V40 stem at 1 year. Secondary aims are to evaluate comparative pre- to post-operative changes in joint-specific function, general health and health economic parameters.

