### Study outcomes and timelines

The trial primary endpoint is the comparative (between-group) change in Oxford Hip Score (OHS) from preoperation baseline to 1 year postoperation. Secondary outcomes are patient-reported outcome measures to evaluate pre- to postoperative changes in joint-specific function, pain, general health and health economic parameters. Radiographic evaluation will focus on stem position and cement mantle evaluation. Clinical complications (thrombosis, dislocation, infection and failure for any reason that results in reoperation) will be recorded.

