### Analysis

#### Sample size

The trial will be an equivalence study, powered on the change in the OHS that is considered clinically significant and of interest when comparing interventions (5 points) [19]. Data from the National Joint Registry indicates that patients typically report a change of 19.7 points (SD 10.4) on the OHS.

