#### Power calculation

A total of 94 participants are required per group to detect a 5-point difference in the primary outcome between groups to achieve and alpha value of 0.05 and beta value of 0.9. Allowing for a potential 15% loss to follow-up we are targeting a total trial recruitment of 220 participants.

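### The primary OHS test is chosen by the observed distribution and left unranked beside a repeated measures ANOVA; as written, only the t test estimates the 1-year mean difference on which the trial was sized.

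*Protocol article*

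**What the plan says.** All places are in the protocol article.

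- **Study aim.** The question is whether the 125 mm stem "achieves an equivalent change in patient-reported pain and function" at 1 year, compared with the 150 mm stem.
- **Study outcomes and timelines.** The primary endpoint is the between-group "change in Oxford Hip Score (OHS) from preoperation baseline to 1 year postoperation".
- **Sample size.** "The trial will be an equivalence study, powered on the change in the OHS". The difference is described as "considered clinically significant and of interest when comparing interventions (5 points"), and the registry figure is that "patients typically report a change of 19.7 points (SD 10.4) on the OHS".
- **Power calculation.** 94 per group, "to achieve and alpha value of 0.05 and beta value of 0.9", and 220 in total after 15% loss.
- **Statistical analysis, primary endpoint.** "Differences between groups will be estimated using the appropriate methodology depending on the distribution of data". The two candidates are a t test and a Wilcoxon test at the 5% level.
- **Statistical analysis, next sentence.** "The patient outcome scores will be assessed with repeated measures analysis of variance (ANOVA) models to account for the repeated data collection time points".
- **Statistical analysis, reporting and safeguards.** Results are to be given as an adjusted mean difference with a 95% confidence interval. A data analysis plan is to be final before data lock, and the analysis is to be blind to allocation.
- **Study assessment schedule, Table 1.** OHS is collected pre-operatively and at 52 and 104 weeks.

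**The concern.** An equivalence conclusion needs one estimate, on the scale of the margin, with an interval to compare with that margin. The protocol gives three routes to an OHS result (t test, Wilcoxon, repeated measures ANOVA), and they do not all estimate the same quantity. The observed distribution decides between the first two. The third covers the same scores over more visits than the primary one, and no sentence ranks it.

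The promised adjusted mean difference does not settle this. Neither a t test nor a Wilcoxon test produces an adjusted difference, and the text does not say which model does, adjusted for what, or at which visit.

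At stake is a conclusion that depends on the route, with the possible error in the unsafe direction. The Background worries that the shorter stem may lead to varus malalignment and worse outcomes. Such harm could fall on a minority of patients. Ranks give less weight to a poor minority than means do, and an average over visits can dilute a 1-year effect.

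**Working it through.** **1. Which quantity the design presupposes.** Inputs: margin 5 and SD of change 10.4 (Sample size); alpha 0.05 and power 0.90, reading the stated beta of 0.9 as power (Power calculation). The article does not use the word margin for the 5 points; that reading is tested here.

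Two one-sided tests on a difference in means, true difference 0:

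n = 2 × [SD × (z(1−α) + z(1−(1−power)/2)) / margin]² = 2 × [10.4 × (1.645 + 1.645) / 5]² = 93.6, so **94 per group**, as stated.

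A two-sided superiority calculation with the same inputs, 2 × [10.4 × (1.960 + 1.282) / 5]², gives 90.9, so 91, and does not match. The trial was therefore sized for equivalence on a mean difference within ±5. With 94 per group the standard error is 10.4 × √(2/94) = 1.517.

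**2. What each route estimates.**

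| Route | Quantity | Comparable with 5 points? |
|---|---|---|
| t test on 1-year change | 1-year mean difference | Yes |
| Wilcoxon | p-value, or at best a Hodges-Lehmann shift | Not directly |
| ANOVA, group main effect | average over the visits modelled | Not directly |
| ANOVA, group-by-visit contrast at 1 year | 1-year mean difference | Yes, but none is named |

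**3. ANOVA main effect.** Take a true 1-year difference of 5 and assume a 2-year difference of 0 to 5.

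- Baseline entered as a response: (0 + 5 + 5)/3 = 3.3, down to (0 + 5 + 0)/3 = 1.7.
- Post-operative visits only: (5 + 5)/2 = 5.0, down to (5 + 0)/2 = 2.5.

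Dilution thus needs either baseline as a response or an effect that fades by year 2, and in both cases the main effect must be taken as the answer.

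**4. Means against ranks.** This is a simulation on assumed data. Scores are normal, rounded and capped at 0 to 48; baseline mean 20 (SD 8); 1-year mean 40 (SD 8); 94 per group; baseline/1-year correlation 0 or 0.5. In one arm 20% of patients score 30 points lower, floored at 0. Without the floor the mean loss would be 0.20 × 30 = 6.

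| | Mean difference | Hodges-Lehmann shift |
|---|---|---|
| Size of estimate | about 5.9 | about 4.4 (correlation 0), 3.5 (correlation 0.5) |
| 90% interval wholly within ±5 | about 1.5% of trials | about 5% (correlation 0), 16% (correlation 0.5) |

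Repeat runs gave 1 to 3% for means, and 5 to 8% and 16 to 19% for ranks. The rank column supposes that ranks are always used.

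**The case against.** **A mean difference is available.** This stands. A t test on 1-year change gives exactly the quantity needed, with an interval, and the article promises an adjusted mean difference whatever the test. A reader might infer that no planned analysis yields a 1-year mean difference; the documents do not support that. What remains is that the promised difference is tied to no model, covariate or visit.

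**Blinding and a pre-lock plan.** A reader might infer that the choice of test can be steered towards a wanted result. The article provides for analysis blind to allocation and a plan finalised before data lock, which limits that. Neither fixes what is estimated: a switch made blind still changes the quantity.

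**The ANOVA may be a second, longitudinal analysis.** This is a fair reading, since the t/Wilcoxon sentence names the primary endpoint and the next sentence speaks of outcome scores generally. The text does not state a rivalry; it leaves the order open. Nor does it say that baseline will be a response. The abstract speaks of change from baseline, and with change scores the 0, 5, 5 case averages to 5.

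**Wilcoxon may seldom be chosen.** A reader might infer that it usually would be. The article names no normality test, and the frequency depends on the assumed shape: with capped normal scores in both arms a Shapiro-Wilk test on 188 changes rejects in about 8 to 18% of trials, and with strongly skewed 1-year scores in about 65 to 84%. The point does not rest on this frequency.

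**The illustration is severe.** It is. It gives the affected arm an SD near 15.8 (correlation 0), against the planned 10.4. A point estimate inside ±5 is also not equivalence, and in this scenario both routes usually fail to declare it.

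**These details belong in the analysis plan.** Covariates, covariance structure and contrasts usually do, and their absence is no fault here. But the article is not silent: it states a distribution-dependent rule and a second, unranked model. A later plan must either inherit that or override it.

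**Conclusion.** The point holds as a badly fixed rule, not as missing detail. The endpoint and the sample size presuppose a 1-year mean difference, and the analysis text allows the primary result to come from a method that does not estimate it. It also leaves an ANOVA over several visits unranked beside that method.

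The consequence is modest in frequency and in the unsafe direction. In the assumed scenario false equivalence rises from about 1.5% with means to about 5 to 16% with ranks. Those figures rest on capped normal scores, a 20% minority scoring 30 points lower, baseline/1-year correlation of 0 to 0.5, a 90% interval, and ranks always being used. The reproduction of 94 rests only on the article's own inputs and on reading 5 points as the equivalence margin. The analysis should be changed, but the defect does not undermine the design or the sample size.

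**What to change.** - **Primary estimator.** Whatever the distribution, use the between-group mean difference in OHS at 1 year, adjusted for baseline OHS and for centre, which is the stratification factor under Randomisation procedures. Use a robust or bootstrap interval if residuals are skewed. An unadjusted t-based interval on 1-year change would also cure the core defect.
- **Decision rule.** Set that interval against ±5 points and state its level. At 94 per group the 90% half-width is 1.645 × 1.517 = 2.50, with power about 90%. The 95% half-width is 1.960 × 1.517 = 2.97, with power about 82%.
- **Wilcoxon.** Keep it as supportive only.
- **Repeated measures model.** Use change or post-operative scores with a group-by-visit term. Say whether it is a secondary longitudinal analysis or the source of the primary 1-year contrast.
- **Reporting.** Tie the promised adjusted mean difference to the named model and to the 1-year visit.

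The cost is wording in the analysis plan, agreed before data lock. No extra patients, visits or data are needed, and standard software suffices.

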## Discussion

The primary aim of CASINO is to evaluate whether differences in the length of femoral stem used results in differences in patient outcomes following total hip arthroplasty. The Exeter V40 is the dominant brand of cemented femoral stem used in the UK with greater than 60% of market share [20]. The stem range has been expanded to include short stem options. Whilst national joint registries collect data regarding the implantable devices, the granularity of implant data is variable and few routinely collate patient outcome scores. To our knowledge, there is no randomized trial evidence to evaluate whether the outcome of 125 mm short stem procedures are equivalent to those following procedures carried with the original 150 mm stem length.

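### The primary test named for this equivalence trial is a test for a difference, and no stated rule compares the reported confidence interval with 5 OHS points

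*Protocol article*

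**What the plan says.** The Study aim asks whether the 125 mm stem "achieves an equivalent change in patient-reported pain and function as the 150 mm Exeter V40 stem at 1 year". The endpoint is set under Study outcomes and timelines: "The trial primary endpoint is the comparative (between-group) change in Oxford Hip Score (OHS) from preoperation baseline to 1 year postoperation". The Sample size section says "The trial will be an equivalence study, powered on the change in the OHS that is considered clinically significant", names 5 points as that change, and gives the variability: "patients typically report a change of 19.7 points (SD 10.4) on the OHS".

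The Power calculation section then changes the language to that of a difference trial: "A total of 94 participants are required per group to detect a 5-point difference in the primary outcome between groups". It sets alpha at 0.05 and labels as beta a value of 0.9 that evidently means power. The sidedness of alpha is not given.

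The Statistical analysis section leaves the choice of test to the distribution of the data, either a t test or a "Wilcoxon test at the 5% significance level to compare the distribution of the primary endpoint between the treatment samples". It adds repeated measures ANOVA for the outcome scores and promises an adjusted mean difference with a 95% confidence interval. It does not mention 5 points, a margin, an equivalence hypothesis, or a rule about where the interval must lie. It says that a data analysis plan will be finalised before data lock. The Discussion opens with a difference aim: "The primary aim of CASINO is to evaluate whether differences in the length of femoral stem used results in differences in patient outcomes".

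**The concern.** The t test and the Wilcoxon test both ask whether the data are compatible with no difference. An equivalence trial asks the reverse: whether differences as large as the margin can be excluded. Failing to reject no difference may only mean that the data are imprecise. Rejecting it may only mean that a small difference was measured precisely. The one test the article names for the primary endpoint is therefore of the wrong kind for the primary objective.

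At stake is the error that matters most here: declaring the short stem equivalent when it is 5 points worse. Under a margin rule that error is capped by design, whatever the sample size. If the difference test is used as the criterion, the error is uncontrolled and grows as follow-up is lost.

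The Wilcoxon branch adds a second mismatch. It compares distributions and does not estimate a mean difference in OHS points, which is the scale on which the 5-point figure is set.

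**Working it through.** **Inputs.** SD of OHS change 10.4 and 5 points (Sample size); 94 per group, alpha 0.05 and 0.9 read as power (Power calculation); 15% loss and 220 in total (Power calculation). Assumed: 5 points serves as a symmetric margin, and the true difference is 0 when power for equivalence is computed.

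**1. Reproduce the plan's figure.**
- Two one-sided tests, one-sided alpha 0.05, power 0.90: n = 2 × [SD × (z₀.₉₅ + z₀.₉₅) / 5]² = 2 × [10.4 × (1.645 + 1.645) / 5]² = 93.64, so 94 per arm. This matches exactly.
- Two-sided difference test, alpha 0.05, power 0.90: n = 2 × [10.4 × (1.960 + 1.282) / 5]² = 90.92, so 91 (92 with the t distribution). This is close, but not 94.

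The sample size therefore fits an equivalence calculation with margin ±5, although the text describes detecting a difference.

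**2. Cut-offs at 94 per arm.** SE = 10.4 × √(2/94) = 1.517. In normal approximation:
- the difference test is non-significant if the observed difference is below 1.960 × 1.517 = 2.97;
- equivalence by 90% interval needs it below 5 − 1.645 × 1.517 = 2.50;
- equivalence by 95% interval needs it below 5 − 2.97 = 2.03.

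Two illustrations:
- Observed 2.7: not significant, yet the 90% interval is 0.20 to 5.20 and the 95% interval is −0.27 to 5.67. Equivalence is not shown.
- Observed 3.5: significant, yet the 95% interval is 0.53 to 6.47. Values inside and outside 5 points both remain possible, so equivalence is not refuted.

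**3. Error rates.** P(non-significant | true difference 5) ≈ Φ(1.960 − 5/SE).

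| Per arm | SE | Normal approximation | t test | Margin rule, 90% / 95% interval |
|---|---|---|---|---|
| 94 (planned) | 1.517 | 9.1% | 9.4% | 5% / 2.5% |
| 60 (assumed heavier loss) | 1.899 | 25.0% | 25.7% | 5% / 2.5% |

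The 60-per-arm row is an assumption outside the plan. With 110 randomised per arm it means 50/110 = 45% loss, against the 15% allowed.

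For a true 3-point difference, inside the margin, at 94 per arm: P(p<0.05) ≈ Φ(3/1.517 − 1.960) = 50.7%, or 50.3% with the t test.

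**4. Power of a margin rule at 94 per arm, true difference 0.** Power = 2Φ(5/SE − z) − 1, with 5/SE = 3.296.
- 90% interval (z = 1.645): 90.1%.
- 95% interval (z = 1.960): 81.8%.
- To reach 90% with the 95% interval: n = 2 × [10.4 × (1.960 + 1.645) / 5]² = 112.4, so 113 per arm, and 226/0.85 = 266 in total.

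**The case against.** Several points on the other side stand.

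- The article promises a mean difference with a 95% interval. If that interval is on the OHS-change scale at 1 year, a reader can compare it with 5 points. It would be too strong to infer that the trial cannot answer its own question: the needed output is promised and only the rule is absent. This also softens the complaint about the Wilcoxon branch.
- Nothing in the article says that a non-significant result will be read as equivalence. A reader might infer it, because the 5% test is the only decision criterion given, but the documents do not state it. Nor do they call 5 points an equivalence margin; they call it a clinically significant change.
- A reader might also infer that the 5-point figure was never used. That is true of the stated analysis but not of the design, since 94 per arm agrees with an equivalence calculation on ±5.
- Choosing the test after looking at the distribution is less worrying than it seems, because the analysis is to be done blind to allocation.
- The Discussion's aim sentence is partly a matter of wording: the same section goes on to ask about equivalent outcomes, and the abstract states the equivalence aim.
- At the planned size the numerical contrast is moderate, 9.4% against 5% or 2.5%. The larger figure needs loss well beyond plan.

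The remaining defence is that the later analysis plan may supply the margin rule. It may, and the absence of detail would be no fault in an article. But the article does not leave the primary test open: it names one, and that one has the wrong null hypothesis. A correct analysis plan would have to depart from it.

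**Conclusion.** The stated primary criterion is wrong as written for an equivalence objective and should be corrected. The conclusion that a difference test neither establishes nor refutes equivalence needs no assumption about how the result would be interpreted.

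The size of the problem does rest on assumptions: that 5 points is the margin, that the SD is 10.4, and that non-significance would be taken as equivalence for want of another criterion. On those terms, false equivalence at a true 5-point difference is 9.4% instead of at most 5% at the planned size, rising to about 26% at an assumed 60 per arm. In the other direction, a stem differing by 3 points would be flagged as different about half the time.

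The sample size itself is sound for an equivalence analysis with a 90% interval. It gives less than the intended 90% power if equivalence is judged by the 95% interval that the article names.

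**What to change.** In Statistical analysis, replace the difference test as primary criterion with: equivalence is concluded if the confidence interval for the 125 mm minus 150 mm difference in mean OHS change at 1 year lies wholly within −5 to +5 points (two one-sided tests). Use one pre-specified mean-based analysis whatever the distribution, with the Wilcoxon test as a sensitivity analysis only.

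State the interval level, because the cost depends on it:
- A 90% interval (one-sided alpha 0.05) fits 94 per arm at 90% power. The change is then wording only, with no extra patients.
- If the 95% interval is kept, restate the power as about 82%. Restoring 90% would take 113 per arm, 266 in total after 15% loss.

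In Power calculation, describe 5 points as the equivalence margin instead of a difference to detect, and give the sidedness of alpha. Align the opening aim sentence of the Discussion with the equivalence objective. Carry the same rule into the data analysis plan before data lock.

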### Randomisation procedures

All eligible participants will be randomised on a 1:1 ratio to either a 125 or 150 mm Exeter V40 stem. Randomisation will be performed by a computer-generated number, stratified by centre using random block sizes. The study centre randomisation code is held by the local principal investigator, and consenting patients are accordingly allocated to treatment arm by the local research team. Implant group allocation is passed onto the clinical teams to coordinate surgery. Patients are blinded to the intervention arm.

Participants are free to withdraw from the study at any point or a participant can be withdrawn by the investigator. If withdrawal occurs, it will be documented on a participant ‘Change of Status’ Form. In the event of withdrawal, patients will be invited to provide final primary end-point data*.*

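### The primary comparison of OHS change uses neither baseline OHS nor centre, and the adjusted difference the article promises has no named source; the cost is precision, not validity

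*Protocol article*

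**What the plan says.** The Protocol article, Study outcomes and timelines, defines the endpoint: "The trial primary endpoint is the comparative (between-group) change in Oxford Hip Score (OHS) from preoperation baseline to 1 year postoperation". Table 1 schedules the OHS pre-operatively and at 52 and 104 weeks, so a baseline value is planned for every participant. Under Randomisation procedures, allocation is 1:1 and "stratified by centre using random block sizes"; there are two centres.

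The Statistical analysis section then makes three statements in sequence:

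- The primary endpoint is compared by a t test or a Wilcoxon, depending on distribution: "test at the 5% significance level to compare the distribution of the primary endpoint between the treatment samples".
- A repeated measures ANOVA is to be fitted to the patient-reported scores because they are collected at several visits.
- The form of the reported estimate is then fixed: "Results will be presented as an adjusted mean difference with its corresponding 95% confidence intervals".

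No adjustment variable is named, and the section does not say whether the two-sample test or the ANOVA model is the primary analysis. A data analysis plan is to be finalised before data lock.

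**The concern.** A two-sample test on change subtracts each patient's baseline in full, which fixes the slope of 1-year OHS on baseline at 1. If the true slope is lower, the change score carries variance that a model with baseline as a covariate would remove. Centre shaped the randomisation but is absent from the test, so the standard error tends to be too large if the centres differ in outcome.

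The paragraph also does not fit together. A t test gives an unadjusted mean difference and a Wilcoxon test gives no mean difference at all, so the promised adjusted estimate must come from somewhere else, and the article does not say where.

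In an equivalence trial the width of the confidence interval decides whether the margin is met. Precision that is available from data already being collected is therefore worth having.

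**Working it through.** **Inputs from the article** (Sample size and Power calculation): difference of interest 5 points, taken here as the margin ±5; SD of change 10.4; alpha 0.05; 90% power (printed as a beta of 0.9); 94 per group.

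**Inputs assumed**, because the article gives neither the separate SDs nor the correlation: baseline SD s0 = 7–9 and 1-year SD s1 = 8–10, with the SD of change held at 10.4.

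**1. The article's own figure.** Two one-sided 5% tests, true difference 0, 90% power:

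n = 2 × [10.4 × (1.645 + 1.645) / 5]² = 93.6, rounded up to 94. This matches exactly.

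The SD used is that of the raw change score, so the sample size was built for an unadjusted comparison.

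**2. Power of the unadjusted test at 94 per group.** SE = 10.4 × √(2/94) = 1.517. Power = 2Φ(5/SE − z) − 1.

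- 90% interval (z = 1.645): 90.1%.
- 95% interval (z = 1.960): 81.8%.

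**3. What baseline adjustment removes.**

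- Variance of change: s0² + s1² − 2·r·s0·s1
- Residual variance after adjusting for baseline: s1²(1 − r²)
- The difference between them is (s0 − r·s1)².

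That difference is a square, so in large samples adjustment is never less precise. It is zero only when r·s1 = s0, that is, when the slope of 1-year OHS on baseline is exactly 1.

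**4. Size under the assumed SDs.** For each pair, r is solved from s0² + s1² − 2·r·s0·s1 = 10.4² = 108.16. Power is by the formula in step 2, with the residual SD in place of 10.4.

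| s0, s1 | r | Residual SD | Variance reduction | Power, 90% CI | Power, 95% CI |
|---|---|---|---|---|---|
| 9, 8 | 0.26 | 7.73 | 45% | 99.5% | 98.7% |
| 8, 8 | 0.16 | 7.90 | 42% | 99.3% | 98.3% |
| 8, 9 | 0.26 | 8.70 | 30% | 97.8% | 95.2% |
| 8, 10 | 0.35 | 9.37 | 19% | 95.6% | 91.1% |
| 7, 10 | 0.29 | 9.57 | 15% | 94.8% | 89.6% |

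The first and last rows are the extremes of the full 3 × 3 grid (SDs in steps of 1), over which r runs from 0.04 to 0.40.

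**5. Outside those SDs.** If s1/s0 = 1.25 and r = 0.7, the reduction is 2%; if s1/s0 = 1.5 and r = 0.7, it is about 0%. With the change SD held at 10.4, these cases need a 1-year SD of about 14.4–14.5. In the other direction, s1/s0 = 0.75 and r = 0.1 gives 61%.

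**6. Centre.** Nothing in the article allows the gain from a centre term to be quantified, so the figures above are for baseline only.

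**The case against.** The strongest reply is that nothing here is invalid. Under randomisation the change-score comparison is unbiased, chance baseline imbalance is already reflected in its standard error, and ignoring a stratification factor tends to make the test conservative. Step 1 shows that the sample size was set for this very analysis. All of that stands. A reader might infer a biased estimate or a power shortfall, and the article supports neither. The 81.8% figure arises only if a 95% interval decides equivalence, which is a separate question about the decision rule.

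Second, a reader might attach a fixed share of lost variance to the trial. The article gives only the SD of change, so any such figure is conditional and its range reaches close to zero.

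Third, a reader might infer that no adjusted estimate is planned. The repeated measures ANOVA may be its intended source. That stands as far as it goes, but the model has no named covariates and is tied to the repeated time points, not to the primary test. With complete data and baseline included among the responses, its baseline-to-1-year contrast is again the difference in mean change.

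Fourth, a reader might take "If there are concerns as to the balance of data in the trial arm, we will run sensitivity analyses" to mean that adjustment of the primary estimate depends on the data. The sentence promises sensitivity analyses only, follows the missing-data sentence and does not mention baseline OHS.

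Finally, the covariate list may properly sit in the data analysis plan, which is not shown. That would excuse an omission. Here, however, the article names a specific test for the primary endpoint, and a better one is available.

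**Conclusion.** The point holds as one of precision and clarity. The named primary test leaves out baseline OHS and centre, and the paragraph does not say which of its analyses is primary or where the adjusted difference comes from. The planned test is valid and adequately powered on the article's own inputs.

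Under the assumed SDs, baseline adjustment lowers the variance by about 15–45% with no extra patients. The gain in power is roughly 5 to 9 percentage points with a 90% interval and 8 to 17 with a 95% interval. These figures rest on the assumed SDs, a true difference of zero, the normal approximation and 94 evaluable patients per group. If the slope of 1-year OHS on baseline were close to 1, the gain would be close to zero, but in large samples there would be no loss.

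**What to change.** Make the primary analysis a linear model of 1-year OHS on stem group, with baseline OHS (continuous) and centre as covariates. Using change as the response gives the same group estimate once baseline is in the model. Take the adjusted mean difference and its confidence interval from this model and compare the interval with ±5. Label the repeated measures model as supportive, and leave the balance-related sensitivity analyses as they are.

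The cost is wording in the data analysis plan before data lock: no new data, no extra patients and no change to the sample size.
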